#### Interim analyses

Interim analyses are not planned.

#### Methods in analysis to handle protocol non-adherence and any statistical methods to handle missing data

The primary outcome will be analyzed according to a modified-intention-to-treat principle: all randomized patients who underwent SCS lead insertion will be analyzed according to their group allocation, irrespective of the treatment they received. Patients with missing outcomes will be treated as not having met the criteria for pain improvement. Missing data will not be imputed. When the case is dropped or patient’s withdrawal, the reasons will be mentioned in detail.

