### Sample size

The study’s sample size is based on the expected difference of the percentage of patients achieving pain improvement between the new and conventional tonic stimulation patterns.

We assumed that the percentages of pain improvement will be 80% for the new stimulation patterns (DTM or FAST) [15, 17] and 50% for the conventional tonic stimulation pattern [25–28] by reviewing the literature. The required sample size was calculated to be 78 cases with a significance level of 0.05, a power of 80%, and 1:1 allocation. Each group (A, B, C, and D) will enroll 20 cases (40 conventional tonic stimulation and 40 new stimulation patterns in Stim-1). Thus, it is possible to secure a power of 0.8 even with the analysis of Stim-1 alone. In addition, considering the insufficient sample size caused by patient detachment during the research process, it is necessary to expand the target number of cases is 23 in each group, resulting in a total sample size of 92 patients in all groups. Assuming, based on past performance, that there are 2–4 cases enrolled in the SCS trial per month, 24–48 patients are expected to be enrolled annually. Therefore, the target number is expected to be reached in 2 to 4 years.

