### Statistical analysis

The primary analysis will be performed after the completion of the SCS trial of the final registered participant. An analysis of the 12-month follow-up period data will be performed at the completion of the 12-month follow-up after the implantation of the final registered participant. Analyses of the 18- and 24-month follow-up period data will be performed at the completion of 24-month follow-up from the implantation of the final registered participant.

The primary outcome analysis will be as follows. Pain improvement will be compared between each stimulation using logistic regression analysis with explanatory variables of stimulation timing (Stim-1, Stim-2), treatment group (new stimulation patterns, conventional tonic stimulation), pre-VAS score for each stimulation pattern, and interaction between stimulation timing and treatment group. The carryover effect will be examined by testing the interaction terms with a significance level of 10%. If there is no carry-over effect, treatment groups will be compared with a significance level of 5%. If a carryover effect is observed, analysis will be performed with data from Stim-1 only.

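### The enlargement to 92 treats dropouts as removed but the analysis counts post-insertion losses as failures, so Stim-1 power is conditional (0.87 with none missing, 0.72 at worst), and the no-imputation rule collides with the per-period VAS covariate

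*Protocol article*

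**What the plan says.** **Sizing (Sample size).** The assumed response rates are 80% for the new patterns and "50% for the conventional tonic stimulation pattern". The section continues: "The required sample size was calculated to be 78 cases with a significance level of 0.05, a power of 80%, and 1:1 allocation". It then plans 20 patients in each of four groups, that is 40 against 40 in the first period, and concludes: "Thus, it is possible to secure a power of 0.8 even with the analysis of Stim-1 alone". To cover dropout it adds that "it is necessary to expand the target number of cases is 23 in each group", or 92 in total. It gives neither a dropout rate nor the timing of losses.

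**Missing data (Methods in analysis to handle protocol non-adherence and missing data).** The primary analysis set is every randomised patient who had leads inserted. The rule for missing values is: "Patients with missing outcomes will be treated as not having met the criteria for pain improvement. Missing data will not be imputed".

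**Model (Statistical analysis).** The primary analysis is a logistic regression on Stim-1 and Stim-2. Its terms are timing, treatment group, their interaction, and "pre-VAS score for each stimulation pattern". If the interaction test indicates carryover, only Stim-1 is analysed.

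**Schedule (Method of SCS trial).** Stimulation starts one day after lead insertion. Each pattern runs for two days, with one day off between patterns, and VAS is recorded before and after every period.

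**The concern.** There are two separate problems.

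1. **The dropout allowance and the analysis use different rules.** Dividing a target by the retained fraction restores power only when lost patients leave the analysis and the response rates among the rest are unchanged. Here a patient lost after lead insertion remains in the denominator and is scored as not improved. With a missing share m in both arms, the difference to be detected shrinks from 0.30 to 0.30(1 − m). Adding patients by the removal formula does not make up for that.

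2. **The missing-data rule and the primary model cannot both be followed for some patients.** The model needs a VAS taken before each period. A patient who leaves before the pre-Stim-2 VAS has neither a Stim-2 outcome nor that covariate. The rule requires the Stim-2 row to count as not improved. The ban on imputation leaves the covariate empty, and a standard logistic fit omits rows with an empty covariate.

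At stake are a power statement that does not say what it depends on, and a fitted analysis set that may differ from the declared modified intention-to-treat set.

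**Working it through.** **Inputs.** From Sample size: rates 0.80 and 0.50, level 0.05, power 0.80, 1:1 allocation, 40 per arm in Stim-1 before enlargement and 46 per arm after it (92/2). Assumptions: a two-sided test, since sidedness is not stated but two-sided reproduces the 78; the same missing share m in both arms; and patients with missing outcomes who would otherwise have responded at the assumed rates.

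**Step 1: reproduce the plan's figures.** Pooled-variance formula, with p̄ = (p1 + p2)/2:

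n per arm = [1.96·√(2p̄(1 − p̄)) + 0.8416·√(p1(1 − p1) + p2(1 − p2))]² / (p1 − p2)²

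With p̄ = 0.65: (1.96 × 0.6745 + 0.8416 × 0.6403)² / 0.09 = 38.5. That rounds up to 39 per arm, or 78 in total, as stated. The corresponding power at 40 per arm is 0.816, which agrees with the stated 0.8.

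**Step 2: what the enlargement assumes.** 80/92 = 0.870, so the implied loss is 12/92 = 13.0%. This share is inferred, because no rate is stated. 80/(1 − 12/92) = 92 is the formula for losses that are removed.

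**Step 3: apply the failure rule.** The rates become 0.80(1 − m) and 0.50(1 − m), and

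power = Φ{[(p1 − p2)√n − 1.96·√(2p̄(1 − p̄))] / √(p1(1 − p1) + p2(1 − p2))}

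At m = 12/92 the rates are 0.696 and 0.435, with n = 46: (1.769 − 1.96 × 0.7011)/0.6764 = 0.584, and Φ(0.584) = 0.72. An exact calculation for the uncorrected chi-square test gives 0.71.

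| Missing Stim-1 outcomes, 92 analysed | Rates | Power |
|---|---|---|
| 0% | 0.800 vs 0.500 | 0.87 |
| 5% | 0.760 vs 0.475 | 0.81 |
| 8% | 0.736 vs 0.460 | 0.78 |
| 10% | 0.720 vs 0.450 | 0.76 |
| 13% (12/92) | 0.696 vs 0.435 | 0.72 |

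The 0.80 line is crossed at about 6%.

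**Step 4: timing of the 12 implied losses.** Losses before insertion leave the analysis set. Losses between insertion and the post-Stim-1 VAS become failures. Later losses do not touch Stim-1.

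| Before insertion | Insertion to post-Stim-1 VAS | After Stim-1 | Analysed per arm | Power |
|---|---|---|---|---|
| 0 | 12 | 0 | 46 | 0.72 |
| 6 | 6 | 0 | 43 | 0.76 |
| 4 | 4 | 4 | 44 | 0.80 |
| 12 | 0 | 0 | 40 | 0.82 |
| 0 | 0 | 12 | 46 | 0.87 |

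**Step 5: the covariate.** For a patient who leaves after the post-Stim-1 VAS but before the pre-Stim-2 VAS:

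- Stim-1 row: outcome and covariate both present, so it is used.
- Stim-2 row: outcome set to not improved by the missing-data rule; covariate absent; filling it barred by the no-imputation sentence.

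The row must be analysed and cannot enter the model as specified. This holds at any dropout rate. It does not apply to someone who leaves during Stim-2, whose pre-period VAS exists.

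**The case against.** **The stated power is not miscalculated.** The 0.8 is attached to 40 against 40, before enlargement, and it reproduces. This stands. A reader might infer that the plan's Stim-1 power simply falls to 0.72, but the document does not support that. It would need every implied loss to fall in the roughly three days from insertion to the post-Stim-1 VAS. Treatment is given in hospital (Strategies to improve adherence to interventions), so few losses may occur then. The Sample size section places no losses in that window, and the 13% is itself inferred.

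**Stim-1 alone is the fallback.** This also stands. The planned primary model uses two periods, and its power cannot be derived because no within-patient correlation is given. No loss of power is shown for it.

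**The two missing-data sentences are loose wording.** Scoring a missing response as failure is a single imputation, so a reader might call the sentences a flat contradiction. They can be read together as no imputation other than the failure rule, and the scoring of a missing primary response is clear. But that reading still leaves the covariate unfilled, so it does not remove the collision.

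**Missing covariates belong in the analysis plan.** Usually so. Here, though, the article itself fixes the covariate, the failure rule and the ban on imputation, and the three do not fit together. It is fair to add that if rows without a pre-period VAS are dropped, patients lost before the pre-Stim-1 VAS do not dilute Stim-1 either, which narrows the relevant window to the two days of stimulation.

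**The covariate remedy is itself imputation.** True; it has to be declared as such.

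**Conclusion.** The point holds in conditional form. The dropout allowance assumes removal while the analysis keeps post-insertion losses as failures. With 92 analysed, Stim-1-only power is 0.87 with no missing Stim-1 outcomes, 0.81 at 5%, and below 0.80 above about 6%. For the 12 implied losses, 0.72 is the floor. Losses that all precede insertion give 0.82, and losses after Stim-1 leave this figure untouched. These values rest on the plan's own 80% and 50%, a two-sided 5% test without covariates, and equal missingness in the arms.

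The collision between the failure rule, the no-imputation sentence and the per-period VAS covariate needs no assumed dropout rate. It affects the two-period primary analysis for any patient who leaves before the pre-Stim-2 VAS, provided the model is fitted in the standard way that omits incomplete rows. Both matters should be settled before the primary analysis.

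**What to change.** 1. **Sample size.** State the expected share of missing outcomes between lead insertion and the post-Stim-1 VAS, and give Stim-1-only power conditional on it (for 92 analysed: 0.87 at 0%, 0.81 at 5%, 0.76 at 10%, 0.72 at 13%).
2. **Missing data.** Replace the two sentences with one rule: a missing primary response counts as not improved; no other outcome data are imputed.
3. **Primary model.** When a later period's pre-VAS is absent, use the pre-Stim-1 VAS as covariate, declared as a covariate fill-in, so that the row is kept. This does not cover a patient with no pre-Stim-1 VAS, so the text should also say how such a patient is handled.
4. **Sensitivity.** Add an observed-case analysis beside the primary one.

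The cost is a less favourable stated power and a little more analysis work. No extra patients are needed.

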#### Plans to give access to the full protocol, participant-level data, and statistical code

The study is registered at Japan Registry of Clinical Trials (jRCT 1042220094). At the end of the study, the full protocol, data, and analysis results will be available from the corresponding author upon reasonable request.

### Oversight and monitoring

#### Composition of the coordinating center and trial screening committee

Nagoya University will serve as the coordinating center. Only the investigators and members of the data center will have access to the anonymized data in the REDCap.

#### Composition of the data monitoring committee, its role, and reporting structure

Two participating researchers at Nagoya University Hospital will monitor the data. They have the responsibility of verifying patients’ eligibility, written, informed consent, compliance with the protocol, and accuracy of the data in REDCap.

#### Adverse event reporting and harms

Adverse events that may be expected in the study population include infection, hemorrhage, nerve damage, and device failure or misalignment. During hospitalization, adverse events will be systematically collected from clinical and radiological examination records and daily nursing reports in the electronic patient records. At the outpatient follow-up visits, adverse events will be collected based on the history and clinical examination. During the study, all adverse events will be recorded in REDCap. A serious adverse event is defined as death, or persistent or significant disability or incapacity that requires hospitalization or prolongation of existing hospitalization. Such serious and all other adverse events will be reported in the final manuscript of the study. Researchers will immediately report serious adverse events associated with the trial to the chief investigator. The chief investigator will then report serious adverse events to the director of the hospital and the principal investigator. Data about all serious adverse events will also be collected in REDCap.

#### Plans for communicating important protocol amendments to relevant parties

Any protocol modifications will be reviewed by the Certified Review Board of Nagoya University Hospital and then registered at jRCT. All relevant information will be shared among the researchers.

#### Dissemination plans

The results of this study will be published in a peer-reviewed journal and presented at national and international medical congresses.

## Discussion

This is a single-center, open-label, crossover, randomized clinical trial to elucidate whether SCS using the latest new stimulation patterns for neuropathic pain provides more pain relief than the conventional tonic stimulation pattern, and which kind of stimulation provides the most pain relief effects for which kind of neuropathic pain.

When assessing the effects of multiple stimulation patterns, there are two main biases. One is the order of stimulation, and the other is residual previous stimulation effects. To eliminate the initial bias, participants will be randomly assigned to 4 groups with different orders of the stimulation patterns (tonic, DTM, and FAST). The order of stimulation will be assessed among 4 respective groups because the study design is a comparison of the latest stimulation patterns and the conventional tonic stimulation. To eliminate the second bias, a 1-day stimulation-off period is set before administering each stimulation pattern to wash out the previous stimulation effects. Since the electrodes are external during the trial, the trial period is set to be within 10 days to avoid the risk of infection. Therefore, the duration of each stimulation pattern is set to 2 days, and stimulation-off is set to 1 day.

In this study, patients with histories of spine or spinal cord surgery at the site through which the SCS lead passes or will be placed will be excluded. The reason is that such patients may have adhesions around past spinal surgeries that make it difficult to pass the cylinder-type leads. Such patients will be enrolled in our other concurrent prospective clinical study [29]. In the concurrent study, treatment success is defined as a greater than 33% improvement in pain relief. Therefore, this study also defines treatment success as a greater than 33% improvement in pain relief in order to maintain consistency between the two parallel studies.

When performing SCS to relieve neuropathic pain, it is common to first evaluate the pain-relieving effects using an SCS trial and then implant the SCS system [4–8]. This two-step procedure is not unique to this study and is actually the method adopted by many clinical practices. The SCS trial is an essential step particularly for central neuropathic pain, such as central post-stroke pain, because the efficacy of SCS for such pain is not yet considered sufficient [25–28]. When performing a fair assessment of SCS efficacy, it is necessary to evaluate the effect in all cases, including non-responders. The primary and secondary outcomes (1) and (2) of this study will be analyzed at the end of the SCS trial to include all cases. However, the secondary outcomes (3) and (4) will be analyzed in relation to the changes in each assessment item over time only for responders, not including non-responders. Therefore, these secondary outcomes are not fair analyses and should be used for reference. To accurately verify long-term SCS effects and identify long-term efficacy predictors, a well-designed, prospective, randomized study with limited causative diseases and stimulation patterns will be necessary.

## Trial status

This manuscript is based on the protocol (version 2, last updated on October 5, 2022). The first patient was recruited on February 20, 2023. Recruitment will be completed by March 2028.

## Data Availability

Any data required to support the protocol can be supplied on request.

## Abbreviations

DTM: Differential target multiplexed
EDC: Electronic data capture
FAST: Fast-acting subperception therapy
IPG: Implantable pulse generator
jRCT: Japan Registry of Clinical Trials
PCS: Pain Catastrophizing Scale
QIDS-J: Quick Inventory of Depressive Symptomatology
REDCap: Research Electronic Data Capture
SCS: Spinal cord stimulation
SF-MPQ-2: Short-Form McGill Pain Questionnaire-2
VAS: Visual analog scale
